## Abstract

**Background:**

Palliative care addresses multiple unmet needs of people with chronic obstructive pulmonary disease (COPD) or interstitial lung diseases (ILD) and their family and/or friend caregivers, but it remains highly underused. Pulmonary rehabilitation (PR) may provide a key opportunity to introduce palliative care. We aim to explore the effects of palliative care education as part of PR on knowledge about this field in people with COPD or ILD and their family and/or friend caregivers.

**Methods:**

A randomized controlled study will compare PR with palliative care education (experimental) with traditional PR (control) in people with COPD or ILD and their family and/or friend caregivers. Family and/or friend caregivers will be invited to take part in education and psychosocial support sessions. In addition to the usual educational content, the experimental group will have a session on palliative care, a “Peer-to-peer session”, two “Get-apart sessions” and online sessions. The “Peer-to-peer session” and the “Get-apart sessions” will be discussions about topics suggested by participants. The “Get-apart sessions” will be dedicated to people with COPD or ILD apart from their family and/or friend caregivers and vice versa. The online sessions will be zoom meetings to discuss any health-related issues raised by participants, at a flexible time. A mixed-methods approach will be used to evaluate the outcomes. The primary outcome will be knowledge about palliative care. Secondary outcomes will include attitude towards palliative care referral, symptoms, disease impact, health-related quality of life, needs, knowledge about the disease, burden of providing care, adherence, adverse events and referral to a specialist palliative care team. Quantitative and qualitative data will be collected at baseline and end of PR. At 6-months post-PR, only patient-reported outcomes will be collected. For the primary outcome, time*group interaction will be analyzed with mixed analysis of variance.

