### Outcomes

The primary outcome will be knowledge about palliative care evaluated with the Palliative Care Knowledge Scale (PaCKS) [45]. Data will be collected at baseline (T0) and end of PR (T1). At 6-months post-PR (T2), only patient-reported outcome measures will be collected. Table 2 provides a detailed description of primary and secondary outcomes that will be assessed throughout the study period. Some outcomes, such as functional capacity, peripheral muscle strength and balance are not expected to be influenced by education, however they are important to assess the effectiveness of PR delivery.

**Table 2 Tab2:** Overview of outcomes and outcome measures evaluated in people with chronic obstructive pulmonary disease or interstitial lung diseases and their family and/or friend caregivers

Outcome	Outcome measure	Description	MCID^a^	People with COPD or ILD	Family and/or friend caregivers	T0	T1	T2
Knowledge about palliative care	PaCKS [45]	- Self-reported questionnaire with 13 items which are true or false. A broad range of topics are assessed, including goals, target population and timing of palliative care, as well as symptoms and problems that palliative care addresses - For each statement, “True”, “False” and “I don’t know” options are provided, and a mark is given for each correct answer - Scores range from 0/13 to 13/13, with higher scores indicating higher knowledge	Not applicable	⬤	⬤	×	×	×
Attitude towards palliative care referral	“Would you like (your loved one) to be referred to a specialist palliative care team at this time?” [46]	- “Would you like to be referred to a specialist palliative care team at this time?” and “Would you like your loved one to be referred to a specialist palliative care team at this time?” will be asked to people with COPD or ILD and their family and/or friend caregivers, respectively - Possible answers are “Yes”, “No” or “Don’t know”	Not applicable	⬤	⬤	×	×	×

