### Sample size calculation

The sample size was estimated for the primary outcome measure, PaCKS, in G*Power 3.1.9.4, for the time*group interaction of a mixed analysis of variance (ANOVA) with two groups (control and experimental) and two timepoints (at baseline and end of PR). We considered an α of 0.05, a power of 0.80, a correlation among repeated measures of 0.5, a nonsphericity correction of 1 and an expected effect size f of 0.25 [76]. The calculated sample size was 34 and considering a possible 40% dropout and missing data rate [77], the final sample size was determined to be 58 (29 in each group).

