### Statistical analysis plan

A mixed-methods approach [78] will be used to explore the effects of the intervention. First, quantitative and qualitative data will be analyzed separately, in a parallel process.

Quantitative data will be processed using IBM SPSS Statistics version 29.0 and RStudio 2022.12.0. Categorical variables will be presented as counts(percentages). Quantitative variables will be summarized using mean ± standard deviation or median[interquartile range], based on the normality of data distribution which will be explored with Shapiro–Wilk test. The EG will be compared with the CG for the primary outcome with a mixed ANOVA if assumptions are met, followed by a multiple pairwise comparison with Bonferroni correction; otherwise, an aligned rank transform-ANOVA will be performed instead. Imputation methods will be used to deal with missing data as appropriate, followed by sensitivity analyses. For all statistical analyses, a *p* value < 0.05 will be considered statistically significant.

Qualitative data will be processed using Web Qualitative Data Analysis (WebQDA) for inductive thematic analysis [79]. The proposed six-step procedure will be followed: 1. familiarizing with the data; 2. generating initial codes; 3. searching for themes; 4. reviewing themes; 5. defining and naming themes; and 6. producing the report [79]. Trustworthiness of the qualitative research will be ensured using the credibility, transferability, dependability, and confirmability criteria [80]. Credibility will be ensured by a) researcher triangulation i.e., each focus group will be transcribed and preliminary coded by one researcher ([name]); then, data will be independently analyzed by two researchers ([name] and AM), which will agree on themes and subthemes; and finally, all the research team ([name], AM and DJ) will review the themes and subthemes until consensus is reached; and, b) engagement with data by all the research team. Transferability will be ensured by a comprehensive and detailed description of the research setting and participants. Dependability will be ensured by having an independent researcher that will examine, explore and challenge the processes of data collection, analysis and interpretation. Confirmability will be ensured by researcher reflexivity, peer debriefing and member checking among people with COPD or ILD and their family and/or friend caregivers.

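### The primary interaction test on PaCKS is valid and correctly sized, but baseline-adjusted ANCOVA on the same data would be more powerful (about 0.89-0.90 against 0.81 at the plan's own correlation)

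*Protocol article*

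**What the plan says.** The abstract fixes the primary test: "For the primary outcome, time*group interaction will be analyzed with mixed analysis of variance". The Statistical analysis plan section agrees: "The EG will be compared with the CG for the primary outcome with a mixed ANOVA if assumptions are met". It adds Bonferroni-corrected pairwise comparisons as a follow-up, and an aligned rank transform ANOVA if assumptions fail. The same section provides for imputation of missing data with sensitivity analyses.

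The Sample size calculation section computes the number for the time*group interaction with two arms and two timepoints, baseline (T0) and end of rehabilitation (T1). Its inputs are "We considered an α of 0.05, a power of 0.80", "a correlation among repeated measures of 0.5" and "an expected effect size f of 0.25". The result is 34, raised to 58 (29 per arm) for 40% dropout and missing data.

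PaCKS, scored 0 to 13, is measured at T0, T1 and six months later (T2) according to Table 2. Nowhere does the article name baseline PaCKS as a covariate.

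**The concern.** With two arms and two timepoints, the interaction contrast is the between-arm difference in mean T1 minus T0 change. Its F statistic is the square of the two-sample t statistic on change.

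Randomisation makes the baseline means equal in expectation, so change scores and baseline-adjusted T1 scores estimate the same treatment effect. Subtracting the whole baseline over-corrects whenever the regression slope of T1 on T0 is below 1. ANCOVA estimates that slope from the data and so has the smaller variance in large samples.

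What is at stake is precision in a small trial. The plan allows for 40% loss, so 58 x 0.6 = 34.8, about 35 evaluable participants. That is just enough for 0.80 power with the planned test, and only if the correlation is at least about 0.5.

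**Working it through.** **Inputs.** From the Sample size calculation section: alpha 0.05, power 0.80, f = 0.25, correlation rho = 0.5, two groups, two timepoints, 40% loss. The 1:1 allocation is in the Study design section. Assumed here: equal variance of PaCKS at T0 and T1 (the article gives no SDs). Values of rho other than 0.5 are also assumptions.

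**1. The plan's own number.** For the within-between interaction, the noncentrality is lambda = f² x N x m / (1 - rho) = 0.0625 x N x 2 / 0.5 = 0.25N, with 1 and N - 2 degrees of freedom.
- N = 33: power 0.795.
- N = 34: lambda = 8.5, power 0.807.

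So 34 is reproduced. Then 34 / 0.6 = 56.7, which gives 57, or 58 for equal arms. That is reproduced too.

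**2. The effect behind f = 0.25.** For a t-test on change with total N and a difference of d SD, lambda = (N/4) x d² / [2(1 - rho)]. Setting this equal to f² x N x 2 / (1 - rho) gives d² = 16f², so d = 4f = 1.0 SD. With d = 1.0, rho = 0.5 and N = 34, lambda = 8.5 / 1.00 = 8.5, the same as in step 1. This confirms that the two tests are the same.

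**3. Variance of the two estimators**, in units of the PaCKS variance:
- change: 2(1 - rho) = 2 x 0.5 = 1.00
- ANCOVA: 1 - rho² = 1 - 0.25 = 0.75
- ratio ANCOVA/change: (1 + rho)/2 = 0.75, a 25% reduction in large samples.

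Estimating the slope adds a finite-sample factor 1 + 1/(N - 4). At N = 34 this is 1 + 1/30, so the ratio is 0.75 x 1.0333 = 0.775, a reduction of about 22%. A 20,000-run simulation gave 0.778.

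**4. Power at 34 evaluable, d = 1.0 SD, rho = 0.5.** ANCOVA has 1 and N - 3 = 31 degrees of freedom.
- Without the factor: lambda = 8.5 / 0.75 = 11.33, power 0.903.
- With the factor: lambda = 8.5 / 0.775 = 10.97, power 0.894.
- Simulation: 0.811 for change, 0.897 for ANCOVA.

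The difference detectable with 80% power falls from 0.99 SD to 0.86 SD (0.87 with the factor). The evaluable number needed for a two-arm trial of equal size falls from 34 to 26 without the factor (power 0.805) and to 28 with it (0.820; at 26 it is only 0.787).

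**5. Dependence on the correlation**, N = 34 and d = 1.0 SD throughout:

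| rho | Large-sample variance reduction | Power, change | Power, ANCOVA (with factor - without) |
|---|---|---|---|
| 0.3 | 35% | 0.67 | 0.83 - 0.84 |
| 0.4 | 30% | 0.73 | 0.86 - 0.87 |
| 0.5 | 25% | 0.81 | 0.89 - 0.90 |
| 0.6 | 20% | 0.885 | 0.93 - 0.94 |
| 0.7 | 15% | 0.95 | 0.97 - 0.98 |
| 0.8 | 10% | 0.994 | 0.996 - 0.997 |

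ANCOVA stays above 0.80 over this range. The planned test does not if rho is 0.4 or less.

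**The case against.** The strongest reply is that nothing in the plan is wrong. The interaction test is unbiased under randomisation, the sample size was computed for exactly that test, and its target of 0.80 is met at 34. This stands: the point concerns efficiency and corrects no error.

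The size of the gain is also uncertain. The article gives 0.5 as its only correlation and offers no PaCKS data to support a lower or a higher value. If the true correlation is 0.7 or 0.8 there is little left to gain. The equal-variance assumption is unverified for a bounded score after teaching in one arm. Both points stand, which is why the range is shown.

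Three stronger readings are tempting, but the article does not support them.
- A reader might infer that everyone without a T1 score is simply dropped despite the expected 40% loss. The Statistical analysis plan section provides for imputation and sensitivity analyses. A plain ANCOVA needs T1 as well, so missing data do not separate it from the planned test.
- A reader might infer that the Bonferroni pairwise comparisons will carry the conclusion. They only follow the ANOVA, and the abstract names the interaction as the primary analysis.
- A reader might take T2 to enter the primary ANOVA, since PaCKS is collected then. The interaction would then have 2 degrees of freedom and would not be a pure change-score test. The analysis section does not list the timepoints, but the sample size section uses T0 and T1 only.

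Finally, the trial is registered and recruitment began in August 2023, so a change of primary test needs a formal, justified amendment. That is a real cost, though a small one.

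**Conclusion.** The point holds as an avoidable loss of efficiency in a valid and correctly sized primary test. For the planned effect, ANCOVA with 34 evaluable participants raises power by about 9 percentage points at the plan's own correlation. If the correlation were as low as 0.3, it would make the difference between an underpowered test and one that still exceeds the target.

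The conclusion rests on three things: T0 and T1 are the only timepoints in the primary test, PaCKS has similar variance at both, and the treatment effect is the 1.0 SD implied by f = 0.25. The change is worth making because the baseline score is already collected and the expected evaluable number leaves almost no margin.

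**What to change.** Before unblinded analysis, and by a dated and justified amendment:
- Make the primary analysis an ANCOVA of T1 PaCKS on arm with T0 PaCKS as covariate. A likelihood-based linear mixed model with a common baseline mean across arms is an acceptable alternative, and it also uses participants with only one observed score.
- State T1 as the primary timepoint, in line with the sample size section.
- Report the adjusted mean difference with its 95% CI.
- Keep the planned imputation and sensitivity analyses, and reword the fallback for failed assumptions so that it matches the new model.
- Keep the 58 participants, with the gain serving as a margin against dropout and a lower correlation than assumed.

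The cost is a short change to the analysis text, the matching sentence in the abstract, and an update of the registration if it names the test. No further data or participants are needed.

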**Discussion:**

This study aims to demonstrate the impact of integrating palliative care into the PR education program.

**Trial registration:**

The trial was registered in the ClinicalTrials.gov U.S. National Library of Medicine, on 1st September, 2023 (NCT06046547).

## Background

Chronic respiratory diseases, including chronic obstructive pulmonary disease (COPD) and interstitial lung diseases (ILD) are among the most common non-communicable diseases worldwide [1]. They are leading causes of mortality and constitute 4.1% of disability-adjusted life-years (DALYs) for all causes, with a significant and increasing individual, societal and economic burden [1, 2].

People with COPD or ILD suffer from physical and psychological symptom burden, multiple limitations in activities and restrictions in participation in daily life, and uncertain expectations about the future, which all have a tremendous impact on their health-related quality of life (HRQoL) [3–8]. Family and/or friend caregivers are their main source of support, throughout the whole disease trajectory [5]. They fulfill many roles such as housekeeping and shopping, encouraging adherence to treatments, assisting to coordinate care across providers and settings, recognizing and managing emergency situations and providing emotional and spiritual support over time [5, 9, 10]. Indeed, they facilitate the overcoming of daily challenges and contribute to improved health outcomes e.g., reduce hospitalizations [10, 11]. So, not surprisingly, caring for a person with COPD or ILD can be highly demanding and has major influence on various domains of family and/or friend caregivers’ lives, including physical, psychological, social and financial [5, 12]. In daily clinical practice, this impact of the caring role is undervalued and not addressed by healthcare professionals. In fact, there is limited literature on interventions that include family and/or friend caregivers of people with COPD or ILD [9, 13–17].

Pulmonary rehabilitation (PR) and palliative care are two multicomponent interventions crucial for people with COPD or ILD irrespective of their prognosis [3, 7, 18, 19]. They have been recognized as “two sides of the same coin” [20], by sharing several key characteristics such as: 1) specific aims of managing symptoms, optimizing functional independence and improving HRQoL; 2) a holistic and person-centered approach; 3) individualized goal setting; 4) family and/or friend caregivers involvement and support; and 5) access based on needs [3, 18]. Differences have also been described, namely in the type of treatment interventions used. For example, exercise training is a core component of PR and infrequently used in palliative care. On the other hand, advance care planning is an important element in palliative care and scarcely discussed in PR, even nowadays [3].

Recognizing family and/or friend caregivers as a cornerstone of the unit of care has been consistently advocated by palliative care in different chronic progressive diseases [7, 21] and is clearly stated in the most recent recommendations for serious respiratory illness [18, 22]. Less explored has been the role of PR to support family and/or friend caregivers [9, 13, 15–17]. To date, only one randomized controlled trial has been performed in this area [17]. This study showed that involving the family in PR improves the coping strategies and the psychosocial adjustment to illness of the whole family (not only people with COPD).

In recent years, universal PR and upstream palliative care have been advocated, based on unmet needs [3, 18, 22]. Needs of patients and family and/or friend caregivers living with COPD or ILD encompass multiple life dimensions and include e.g., validation and support throughout the disease, public awareness, need to act and be treated normally, meeting others in similar circumstances, coping strategies, open communication, be included in decision-making, understand the disease, strategies for social participation, support from others but allowing autonomy and medication management/equipment handling [5, 6, 23, 24]. However, palliative care remains highly underused in people with chronic respiratory diseases [18]. One of the reasons reported is the unclear awareness of the potential role of palliative care allied to inadequate knowledge and misperceptions of this field among patients [18, 25, 26].

PR could be an ideal setting to identify and assess unmet needs of people with COPD or ILD and their family and/or friend caregivers and introduce palliative care [3, 19, 27]. Education and psychosocial support sessions are a well-established component of PR. Including palliative care educational content (e.g., concept, role and goals of palliative care, symptom control, disease impact, psychosocial support and planning for the future) in these sessions and actively involving family and/or friend caregivers represents an important opportunity to introduce palliative care in PR. Indeed, already a decade ago advance care planning was mentioned as one of the educational topics in PR [28], which has been well received by patients [29]. Moreover, across the PR program, individuals could be timely referred to a specialist palliative care team, which has the potential to add particular benefit in breathlessness management, advance care planning and psychosocial support. Another possible strategy to improve patients’ and family and/or friend caregivers’ care is educating and training rehabilitation staff in palliative care issues and advanced communication skills [3, 7, 22, 27]. In fact, placing focus on palliative care in PR has the potential to provide the best chance of timely addressing unmet needs of those with COPD or ILD and their family and/or friend caregivers. However, the direct effects of this integrated care model on patients’ and family and/or friend caregivers’ outcomes have not been studied before.

We hypothesize that by integrating palliative care education in PR for people with COPD or ILD and their family and/or friend caregivers we will improve knowledge about palliative care. Furthermore, we hypothesize that by enhancing educational opportunities, namely including the topic of palliative care in PR we will change the attitude towards palliative care referral, improve symptoms, disease impact, HRQoL, needs, knowledge about the disease and reduce burden of providing care.

The primary aim of this study is to explore the effects of palliative care education as part of PR on people with COPD or ILD and their family and/or friend caregivers’ knowledge about palliative care. Secondary aims are to: a) understand the perspectives of people with COPD or ILD and their family and/or friend caregivers about integrating palliative care education in PR; and b) explore the effects of PR with more educational opportunities, namely including the topic of palliative care on people with COPD or ILD and their family and/or friend caregivers’ attitude towards palliative care referral, symptoms, disease impact, HRQoL, needs, knowledge about the disease and burden of providing care.

This article describes the study protocol in detail and provides an overview of its strengths and limitations.

## Methods

### Study design

A randomized controlled study to compare PR with palliative care education (experimental) with traditional PR (control) in people with COPD or ILD and their family and/or friend caregivers has been deigned. The study was registered in the ClinicalTrials.gov U.S. National Library of Medicine (NCT06046547) and will follow the Consolidated Standards of Reporting Trials (CONSORT) statement for nonpharmacological treatments [30], Template for Intervention Description and Replication (TIDieR) checklist and guide [31], Consolidated Criteria for Reporting Qualitative Research (COREQ) guidelines [32] and Good Reporting of A Mixed Methods Study (GRAMMS) framework [33].

Participants will be randomized into an experimental group (EG) and a control group (CG), using a 1:1 allocation ratio and random block sizes of two and four. An independent researcher will use an online software tool (https://www.sealedenvelope.com/simple-randomiser/v1/lists) to generate a computer-based random allocation list and will inform the lead researcher ([name]) about their group allocation via phone call.

Assessors and the researcher responsible for moderating the focus groups will not be involved in PR provision and will be blinded to group allocation. Participants and the researcher conducting the intervention will not be blinded to group allocation, due to the nature of the intervention. The blindness of the researcher performing the data analysis will be ensured by anonymizing all data.

### Participants

People with COPD or ILD and their family and/or friend caregivers will be recruited from the outpatient pulmonary rehabilitation unit at Centro Hospitalar do Baixo Vouga (CHBV), a secondary hospital. Recruitment started in August 2023, with final data collection expected to be completed in June 2026. The pulmonologist of the PR program will identify eligible participants and explain the study. Patients will be eligible if they are adults with a diagnosis of COPD according to the Global Initiative for Chronic Obstructive Lung Disease (GOLD) criteria [34] or with a multidisciplinary diagnosis of ILD [35] and are clinically stable in the previous month (i.e., without acute exacerbation). Patients will be excluded if they present a musculoskeletal, neurological or psychiatric condition which may limit their participation in PR, had participated in any PR program in the last 6 months, had received specialist palliative care in the last 12 months or are unable to understand Portuguese. Family and/or friend caregivers will be eligible if they are adults identified by the participating people with COPD or ILD as caregivers. For this purpose, it will be explained to people with COPD or ILD that a family and/or friend caregiver is any relative, partner, friend, neighbor, or significant other with personal relationship with them, and who provides a broad range of unpaid assistance, namely with activities of daily living (e.g., toileting, feeding and bathing) and instrumental activities of daily living (e.g., shopping, meal preparation and managing finances)] [36]. Family and/or friend caregivers will be excluded if they present a neurological or psychiatric condition which may limit their participation or are unable to understand Portuguese. An appointment with those willing to participate will be scheduled to clarify any doubts, gather informed consents and conduct baseline assessments.

